#### Acute medication use

Measurement: Change in the number of days of acute migraine medication use per menstrual cycle.

Tool: Electronic daily headache diary within the ePRO system. Permitted rescue medications are pre-specified.

Assessment Timepoints: Baseline, Treatment Months 1–3, and 3-month post-treatment follow-up.

Analysis: Total number of days of acute medication use per cycle will be summarized, and between-group changes from baseline will be evaluated.

#### Core autonomic function parameters

Measurement: Changes in heart rate variability (HRV) indices, reflecting cardiac autonomic modulation.

Procedure: Standardized 5-min supine resting HRV recording will be performed in a quiet, temperature-controlled room following a 15-min acclimation period.

Equipment: High-fidelity, FDA-cleared single-lead electrocardiogram (ECG) monitor with a sampling rate ≥500 Hz.

Assessment Timepoints: Baseline, Treatment Months 1–3, and 3-month post-treatment follow-up.

Analysis: Raw ECG data will undergo artifact correction and spectral analysis using specialized software. Primary HRV metrics include:

Time-domain: Standard Deviation of NN intervals (SDNN, ms);

Frequency-domain: Low-Frequency power (LF, 0.04–0.15 Hz), High-Frequency power (HF, 0.15–0.40 Hz) in normalized units, and LF/HF ratio.

### Exploratory outcomes

#### Mechanistic biomarkers (blood)

Sample Collection: Peripheral venous blood samples (≈10 mL) will be collected at two phase-specific timepoints per menstrual cycle to account for hormonal fluctuations:

Early follicular phase (menstrual days 2–4);

Mid-luteal phase (≈7 days prior to next expected menstruation, confirmed by cycle tracking or urinary luteinizing hormone kits).

Assessment Timepoints: Baseline and end of Treatment Months 1–3.

Sample Processing and Storage: Blood samples will be centrifuged at 4 °C within 30 min of collection. Serum and plasma aliquots will be stored at −80 °C in a dedicated biobank until batch analysis to minimize inter-assay variability.

Biomarker Analysis: Validated commercial assay kits will be used for quantitative detection:

Calcitonin Gene-Related Peptide (CGRP): High-sensitivity enzyme-linked immunosorbent assay;

Estradiol (E2) and Progesterone (P4): Electrochemiluminescence immunoassay on an automated clinical analyzer.

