## Introduction

Menstrual migraine (MM) is a neurological disorder with a high prevalence that significantly impacts women’s lives; it is characterized by migraine attacks concentrated around the menstrual period. According to the International Classification of Headache Disorders, 3rd Edition (ICHD-3), MM can be subdivided into two distinct types: pure menstrual migraine (PMM, Appendix code A1.1.1) and menstrually-related migraine (MRM, Appendix code A1.1.2). PMM is defined as migraine attacks occurring exclusively between the second day before menstruation and the third day after menstruation in at least two of three consecutive menstrual cycles, with no attacks at other times during the menstrual cycle. MRM refers to attacks that occur both within this perimenstrual window and at other times of the cycle in at least two of three cycles (1). These two subtypes reflect fundamentally different temporal patterns of estrogen-withdrawal susceptibility and trigeminovascular sensitization. Epidemiological studies indicate that up to 60% of female migraineurs experience menstrual-related attacks, which are often more severe, longer in duration, and less responsive to conventional acute medications compared to non-menstrual migraines (2). These headaches substantially impair daily functioning, reduce quality of life, and contribute to absenteeism and socioeconomic burden (3).

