The pathophysiological mechanisms of MM involve multiple factors and are primarily driven by a sudden drop in estrogen levels. This process modulates serotonergic and glutamatergic neurotransmission, triggers the release of calcitonin gene-related peptide (CGRP), and exacerbates cortical hyperexcitability and central sensitization (4, 5). Given the predictability of attack timing, short-term perimenstrual prophylaxis (SPP) is the recommended management strategy. International guidelines, including those from the European Headache Federation, identify naproxen sodium as the first-line drug choice for SPP, as it has recognized efficacy in reducing the frequency and severity of menstrual migraines through potent inhibition of peripheral and central cyclooxygenase-2 (6). However, long-term use of naproxen and other nonsteroidal anti-inflammatory drugs (NSAIDs) is associated with gastrointestinal intolerance, an increased risk of bleeding, and the potential to induce medication-overuse headaches (7, 8). This highlights an unmet medical need for the development of safe, well-tolerated, and effective preventive treatment options.

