### Primary outcome

The primary outcome measure is the change in headache frequency, defined as:

Measurement: The mean change in the number of moderate-to-severe headache days per menstrual cycle from baseline (defined as the average across all qualified cycles during the 3-cycle screening period) to the end of the 3-month intervention period. Definition: A headache day is defined as any calendar day on which the participant experiences a headache meeting ICHD-3 criteria for migraine without aura (ICHD-3 code 1.1) with a peak pain intensity of ≥4 on the 0–10 Numeric Rating Scale (NRS, where 0 = no pain, 1–3 = mild, 4–6 = moderate, and 7–10 = severe; thus an NRS score of ≥4 captures both moderate and severe intensity levels). Data Source: Prospectively captured using a validated, electronic daily headache diary.

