#### Comprehensive mechanism analysis

Correlation analysis using Pearson or Spearman will explore the relationships among the following items: changes in major clinical indicators, such as the number of days with moderate to severe headache; core autonomic nerve indicators, such as the LF/HF ratio; serum biomarker levels, such as calcitonin gene-related peptide, estradiol, P4; and indicators derived from neuroimaging, such as the functional connectivity strength in the target network.

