#### Exploratory and safety analyses

Exploratory Biomarkers/Imaging: Changes in serum biomarker levels (CGRP, estradiol, progesterone) and neuroimaging metrics will be analyzed using paired t-tests or Wilcoxon signed-rank tests within each group, and between-group comparisons will be made using ANCOVA. Correlation analyses (Pearson’s or Spearman’s) will explore relationships between clinical, autonomic, and biomarker/imaging changes. All exploratory findings will be reported with effect sizes and 95% CIs, and will be explicitly labeled as “exploratory, unadjusted for multiple comparisons, for hypothesis generation only” to prevent overinterpretation.

Safety Analyses: The incidence of adverse events (AEs) and serious adverse events (SAEs) will be summarized by treatment group, described by system organ class and preferred term. Differences in AE rates will be compared using Fisher’s exact test.

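### The days 2–4 CGRP draw largely overlaps the menstrual attack window and headache state at the draw is not considered, so CGRP can track headache occurrence without any effect between attacks

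*Protocol article*

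**What the plan says.** The section on blood biomarkers sets "two phase-specific timepoints per menstrual cycle to account for hormonal fluctuations". The first is "Early follicular phase (menstrual days 2–4" and the second is "Mid-luteal phase (≈7 days prior to next expected menstruation, confirmed by cycle tracking or urinary luteinizing hormone kits". The section on biological specimens repeats both draws for the baseline and post-intervention samples.

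The Introduction defines pure menstrual migraine by "migraine attacks occurring exclusively between the second day before menstruation and the third day after menstruation". It also says that the estrogen drop "triggers the release of calcitonin gene-related peptide (CGRP".

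Under Exploratory and safety analyses, biomarker changes are tested within each arm and "between-group comparisons will be made using ANCOVA". Comprehensive mechanism analysis correlates biomarker levels, CGRP among them, with "changes in major clinical indicators, such as the number of days with moderate to severe headache". These sections do not mention headache state or recent rescue medication at the draw. Headache days themselves are "Prospectively captured using a validated, electronic daily headache diary", and rescue use is entered in the same diary.

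**The concern.** The draws are timed for hormonal phase only. At days 2–4 some women will be sampled on a headache day, or after rescue medication, and others will not. A treatment that reduces headache days also reduces the share of samples taken during an attack. If CGRP is higher in attacks, its mean falls for that reason alone, and its change follows the change in headache days.

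The third objective is to explore mechanism through such markers. A lower CGRP in one arm, or a correlation with headache days, could be presented as a mechanistic finding when it partly restates the clinical outcome. The planned label on exploratory results warns about multiplicity and hypothesis generation. It does not warn about this, and a later trial with the same sampling would reproduce it.

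**Working it through.** **The plan's own figure.** The only sample-size figure is 30 evaluable per arm with 20% dropout: 30 / (1 − 0.20) = 37.5, rounded up to 38 per arm, 76 in total. It reproduces and is not in dispute. It supplies n = 30 per arm below. The protocol gives no CGRP figure to reproduce.

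**Draw days against the window.** Count the onset of menses as day 1.
- If the window ends on day 3, draw days 2 and 3 are inside and day 4 is outside.
- If it ends three days after onset, or three days after menses ends, all three draw days are inside.

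**Arm difference in closed form.** Let E be the rise in CGRP during an attack, in SD of CGRP outside attacks. With no treatment effect outside attacks, the induced difference = E × (attack share at the draw in arm B − attack share in arm A).

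**Simulation.** There were 2,000 runs per setting, with 30 per arm and no treatment effect on CGRP outside attacks. The following are assumptions, not protocol figures: E of 0, 0.5 or 1; about 5 headache days per cycle at baseline, 60% of them in a 5-day window; within-person CGRP correlation 0.5. About 57–58% of baseline draws then fall on a headache day.

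| Headache-day reduction, A vs B | Attack share at draw, A vs B | E | ANCOVA arm difference (SD) | Rejection at 0.05 | Correlation of changes |
|---|---|---|---|---|---|
| 40% vs 40% | 0.35 vs 0.35 | 0.5 | 0.00 | 5.0% | 0.13 |
| 40% vs 40% | 0.35 vs 0.36 | 1.0 | 0.00 | 4.5% | 0.23 |
| 50% vs 30% | 0.30 vs 0.41 | 0.5 | −0.06 | 4.9% | 0.14 |
| 50% vs 30% | 0.29 vs 0.41 | 1.0 | −0.11 | 6.9% | 0.24 |
| 60% vs 20% | 0.24 vs 0.46 | 0.5 | −0.11 | 8.5% | 0.14 |
| 60% vs 20% | 0.24 vs 0.46 | 1.0 | −0.22 | 12.3% | 0.25 |

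The closed form agrees: 0.5 × (0.46 − 0.24) = 0.11 and 1.0 × (0.46 − 0.24) = 0.22. With E = 0 the arm difference and the correlation are both about 0.

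**Does headache state account for it?** With headache state at both draws in the ANCOVA, the arm difference is within about 0.01 SD of zero and rejection is 3.5% to 5.1% (E = 0.5 or 1). With the attack component removed from CGRP, the correlation is about 0. The partial correlation proposed below was not itself simulated.

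**The case against.** Several objections have force.

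- **A reader might infer that CGRP will differ between arms.** The documents do not support that. They give neither a size for a rise during attacks nor attack shares by arm. With equal headache reduction there is no arm difference. With 50% against 30%, rejection stays at 4.9% to 6.9%, close to nominal. With 60 evaluable women, r must reach about 0.25 for p < 0.05, so most of the correlation range would usually not be significant.
- **A reader might infer that any days 2–4 difference is an artefact.** The Introduction places CGRP release upstream, as a consequence of the estrogen drop. Lower CGRP in the better arm could therefore be part of a real treatment effect, and adjusting for headache state could remove some of it. This stands, and it is why adjustment belongs in a sensitivity analysis.
- **A reader might conclude that the mid-luteal sample should lead.** It lies outside the perimenstrual window, but menstrually-related migraine can also produce attacks then. Press-needle sessions fall 5–7 days before expected menses, while naproxen starts only 2–3 days before. A mid-luteal contrast about 7 days before menses thus carries its own asymmetry between arms.
- **The article is condensed.** A sampling manual or analysis plan, not shown, might record headache state, and the article does not say that the two draws are pooled. But it does fix the draw days, the between-arm test and the correlation, and the problem comes from combining them.
- **The outcome is exploratory.** That limits the consequences. The primary outcome and safety are not affected.

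**Conclusion.** The point holds in conditional form. At least days 2 and 3 of the days 2–4 draw lie inside the protocol's attack window, and no stated analysis takes headache state into account. As written, a CGRP difference or correlation from this draw cannot be separated from a change in how many samples were taken during an attack.

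For assumed rises of 0 to 1 SD, the size is about 0 to 0.2 SD between arms and r about 0 to 0.25. The arm difference needs both a rise during attacks and unequal headache reduction. The correlation needs only the rise, so it is the more exposed of the two analyses. All these sizes rest on assumed inputs.

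Extending the point to HRV and MRI would go further than the documents allow: their sections fix no menstrual phase for those sessions, so the overlap with the attack window cannot be shown.

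**What to change.** In Comprehensive mechanism analysis and in Exploratory and safety analyses:

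1. Analyse the days 2–4 and mid-luteal samples separately, not pooled.
2. Classify each draw from the e-diary by calendar day: headache or headache-free, and with or without rescue medication that day or the day before.
3. Report CGRP by draw phase and headache state.
4. Add a sensitivity ANCOVA and a partial correlation that include headache state at both the baseline and the post-treatment draw.
5. State that the unadjusted days 2–4 result may reflect attack occurrence and, in the control arm, current naproxen dosing, which overlaps those days. It is not by itself evidence of mechanism.

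Step 4 needs one agreed pair of draws. The biomarker section (baseline and Months 1–3), the recruitment process (each qualified screening cycle) and the specimen section (last screening and third treatment cycle) differ on which cycles are sampled and must be reconciled.

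The cost is analysis wording, because the diary is already planned. There are two limits to state. Headache state at the post-treatment draw is a post-randomisation variable that may lie on the treatment pathway. The documents also describe diary data by calendar day, with no clock times, so a headache day does not prove an attack at the moment of sampling. The adjusted analysis therefore supports the main contrast and does not replace it.

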#### Neuroimaging markers

Procedure: Structural and functional brain MRI will be performed at baseline and end of the 3-month intervention.

Image Acquisition: All scans will be conducted on a 3.0 Tesla MRI scanner using a standardized protocol, including:

High-Resolution 3D T1-Weighted Imaging: For voxel-based morphometry (VBM) analysis to evaluate regional gray matter volume changes in pain-processing (e.g., insula, anterior cingulate cortex) and autonomic regulation (e.g., hypothalamus, brainstem) regions;

Resting-State Functional MRI (rs-fMRI): 8-min eyes-closed scan optimized for blood-oxygen-level-dependent (BOLD) signal detection.

Assessment Timepoints: Baseline and end of Treatment Months 1–3.

Image Analysis: Preprocessing (motion correction, spatial normalization, smoothing) and statistical analysis will follow standard pipelines. Seed-based correlation analysis and independent component analysis (ICA) will evaluate functional connectivity alterations within/between the Salience Network and Central Autonomic Network.

#### Comprehensive mechanism analysis

Correlation analysis using Pearson or Spearman will explore the relationships among the following items: changes in major clinical indicators, such as the number of days with moderate to severe headache; core autonomic nerve indicators, such as the LF/HF ratio; serum biomarker levels, such as calcitonin gene-related peptide, estradiol, P4; and indicators derived from neuroimaging, such as the functional connectivity strength in the target network.

#### Assessment of treatment credibility and expectations

At baseline, validated scales (such as the Credibility/Expectancy Questionnaire) will be used to assess participants’ credibility and expectations regarding their assigned treatment. This assessment will be conducted after randomization and before the first treatment session. The questionnaire consists of two subscales: credibility (how reasonable and helpful the treatment appears) and expectations (the extent of improvement the participant anticipates). These scores will be used in exploratory analyses to examine whether baseline expectations moderate treatment response and will be included as covariates in sensitivity analyses to control for potential bias.

### Safety outcomes

All adverse events (AEs) and serious adverse events (SAEs) were recorded from the time of signed informed consent until the 3-month follow-up after intervention. The occurrence time, symptoms, severity, duration, management, outcome, and causality with interventions were documented in detail.

Sequential press-needle group: Local skin reactions at the press-needle insertion sites were mainly monitored, including redness, itching, pain, rash, infection, and bleeding.

Oral naproxen sodium group: Adverse reactions related to NSAIDs were intensively monitored, including gastrointestinal reactions (nausea, stomachache, acid reflux, abdominal distension, gastrointestinal discomfort), neurological reactions (dizziness, headache, fatigue), skin allergy (rash, itching), and abnormal liver and renal function.

All systemic AEs were recorded in both groups. The incidence, severity, and causality of AEs were compared between groups to comprehensively evaluate the safety of the interventions.

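### Adverse events are monitored differently by arm and then compared by Fisher's exact test, which shifts the comparison of shared symptoms in favour of press-needle

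*Protocol article*

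**What the plan says.** The Safety outcomes section of the protocol article sets the monitoring arm by arm. For press-needle: "Local skin reactions at the press-needle insertion sites were mainly monitored, including redness, itching, pain, rash, infection, and bleeding". For naproxen: "Adverse reactions related to NSAIDs were intensively monitored, including gastrointestinal reactions". Five gastrointestinal items follow, and then "neurological reactions (dizziness, headache, fatigue), skin allergy (rash, itching), and abnormal liver and renal function".

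The section adds: "All systemic AEs were recorded in both groups". It states that AE incidence, severity and causality are compared between groups. The Exploratory and safety analyses section names the method: "Differences in AE rates will be compared using" Fisher's exact test. Statistical methods sets two-sided significance at 0.05.

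Blinding design states that the trial is open-label for participants and providers. Adverse event reporting and harms gives the causality judgement to the principal investigator.

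**The concern.** A between-arm comparison of AE rates is interpretable only if an event has the same chance of being found in each arm. Here most of the symptoms named for close attention under naproxen could equally occur under press-needle, where attention is directed mainly to the skin. An event that is asked about in one arm and only volunteered in the other will be counted at different rates even when its true frequency is the same. Fisher's test takes the counts as given and cannot correct this.

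Headache is a special case. It is the disease under study and the basis of the primary outcome, yet it is a listed reaction for naproxen only. The article gives no rule that separates an ordinary migraine day from a headache AE.

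Safety and tolerability are stated aims of this pilot, and the Discussion already describes press-needle as the better tolerated treatment. A comparison tilted by how events are looked for would appear to confirm that statement and would carry into the planning of the confirmatory trial.

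**Working it through.** **1. Event types set side by side** (from Safety outcomes)

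| Event type | Can occur in | Named for press-needle | Named for naproxen |
|---|---|---|---|
| Insertion-site reactions | press-needle only | yes | no |
| Rash, itching | both | yes, at the site | yes |
| Gastrointestinal symptoms (five items) | both | no | yes |
| Dizziness, fatigue | both | no | yes |
| Headache | both | no | yes |
| Liver or renal abnormality | both | no | yes |

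Looking for site reactions finds true events of one treatment and distorts nothing. The distortion can arise in the last four rows, and in each of them the closer search is in the naproxen arm.

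**2. Sample size, from the Sample size section.** 30 evaluable per arm with 20% dropout: 30 / (1 − 0.20) = 37.5, rounded up to 38 per arm, 76 in total. This reproduces the plan's figure. Both 30 and 38 per arm are used below. The plan gives no figure for the AE comparison itself.

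**3. Size of the shift.** AE rates and capture probabilities are not in the document, so these are assumptions. Observed rate = true rate × capture probability, with the same true rate in both arms.

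- Naproxen: 0.20 × 0.90 = 18%.
- Press-needle, capture 0.70: 0.20 × 0.70 = 14%, a spurious difference of 4 points.
- Press-needle, capture 0.50: 0.20 × 0.50 = 10%, a spurious difference of 8 points. With 38 per arm that is 38 × 0.08, or about 3 participants.

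**4. Chance of a false result.** Let i and j be the numbers with an event under press-needle and naproxen. P(false result favouring press-needle) is the sum of Bin(i; n, press-needle rate) × Bin(j; n, naproxen rate) over all pairs with i < j and two-sided Fisher p < 0.05. Exact enumeration, with naproxen capture at 90% throughout, gives:

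| True rate, both arms | Press-needle capture | Spurious difference | n = 30 | n = 38 |
|---|---|---|---|---|
| 20% | 90% | 0 points | 1.0% | 1.3% |
| 20% | 70% | 4 points | 2.6% | 3.8% |
| 20% | 50% | 8 points | 6.3% | 10.0% |
| 30% | 70% | 6 points | 4.4% | 5.6% |
| 30% | 50% | 12 points | 12.7% | 17.7% |
| 50% | 70% | 10 points | 7.5% | 9.5% |
| 50% | 50% | 20 points | 27.2% | 36.4% |

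With unequal capture, the chance of a false result in the other direction (favouring naproxen) is at most 0.3% in every case. The error is therefore one-sided, not just larger.

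**The case against.** The strongest reply is that all AEs are to be recorded, and that systemic AEs are recorded in both arms. Table 2 has one AE-monitoring row with the same timepoints for everyone, and Data collection and management mentions safety forms without arm-specific versions. No section says how symptoms are elicited, and form content is commonly left to a full protocol. This stands in part: the capture probabilities are unknown, and a common form may exist. But recording is not elicitation, and the point does not rest on an omission. The article positively directs different attention to the two arms. Blinded assessors do not resolve it either, since arm-specific monitoring can be carried out only by someone who knows the arm.

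A second reply is that press-needle has close surveillance of its own: daily site inspection (Needle retention), immediate reporting (Adverse event monitoring) and documentation of immediate events (Treatment fidelity and environmental control). This stands. A reader might infer that the overall AE comparison must come out in favour of press-needle. The documents do not support that, because true site reactions could make the any-AE rate higher in that arm.

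Other stronger readings also fail:

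- AEs "were recorded from the time of signed informed consent until the 3-month follow-up after intervention", and consent precedes a screening phase of about 12 weeks. A reader might infer that events before randomisation add to the bias. They fall on both arms alike, Table 2 has no AE tick at baseline, and the analysis section does not say that they are counted.
- A reader might infer that nearly every naproxen participant would be logged with a headache AE. Headache is listed among NSAID-related reactions and is subject to a causality assessment, so this does not follow.
- A reader might infer that superior tolerability is the stated hypothesis. Objectives says only that tolerability will be good; the comparative claim is in the Discussion.

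Finally, the plan treats all results as descriptive and preliminary. That limits the consequence but leaves the shift in the estimate.

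**Conclusion.** The point holds for event types that can occur in either arm: gastrointestinal symptoms, dizziness, fatigue, headache and laboratory abnormalities. Following the text as written, in an open-label trial, would move the observed difference in these events in favour of press-needle relative to the true difference. It does not predict the sign of the overall any-AE difference.

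The size cannot be derived from the document. With an assumed true rate of 20% in both arms and 90% capture under naproxen, press-needle capture of 70% to 50% gives a spurious 4 to 8 points. A false Fisher result favouring press-needle then occurs in about 3% to 10% of trials with 30 to 38 per arm, against about 1% with equal capture. Higher true rates give larger figures. The point should be corrected, because tolerability is one of the things the pilot is meant to measure and the remedy is cheap.

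**What to change.** - Use one structured AE checklist (skin, gastrointestinal, neurological, allergy) with the same wording at the existing visits in both arms.
- State one rule, identical in both arms, for when headache counts as an AE. It must be reconciled with Criteria for discontinuation of intervention, where significant worsening of headache is a listed criterion. Excluding all non-serious headache from AEs would go too far for that reason.
- Restrict the between-arm Fisher test to events that are elicited identically and start after randomisation. The second condition only reconciles the recording window in Safety outcomes with Table 2; it does not address the bias.
- Report insertion-site events, and any laboratory findings obtained in one arm only, descriptively and outside the test.

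The cost is one common form and a few sentences of text. No extra visits or tests are needed.

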### Blinding design

This is an open-label trial. Participants and intervention providers will be aware of the group assignments. To avoid detection bias, outcome assessors and statisticians will remain completely unaware of the group assignments throughout the trial. The following measures will be taken to maintain blinding:(1) Blinded outcome assessors: All outcome assessments will be conducted by trained assessors who were not involved in randomization or treatment administration. Participants will be instructed not to disclose their treatment group to the assessors during any assessment visit;(2) Blinded statisticians: Randomization codes will not be disclosed to the statisticians until the final data lock-in and completion of all pre-specified analyses. The dataset provided to the statistician will include coded treatment indicators (e.g., Group A and Group B) but will not reveal the correspondence to the actual interventions;(3) Data manager blinding: Data managers will use coded group identifiers to process and clean the data. They will not have access to randomization information.

To evaluate the influence of the open-label design, participants’ treatment credibility and expectancy will be assessed at baseline and explored as potential confounders in the analysis of treatment effects.

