#### Quality control

Standardized Training: All investigators and research staff will undergo protocol-specific training prior to trial initiation, covering recruitment procedures, intervention protocols, outcome assessment, data entry, and Good Clinical Practice (GCP) guidelines.

Treatment Fidelity: Acupuncturists will follow a detailed treatment manual. Random audits of treatment sessions (e.g., photo verification of point location) will be performed.

Data Monitoring: An independent Data Monitoring Committee (DMC) is not established for this low-risk trial. Instead, the principal investigator and study coordinator will perform regular internal data reviews for completeness, consistency, and protocol adherence.

Protocol Adherence: Regular investigator meetings will be held to discuss protocol adherence and address any operational issues.

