#### Adverse event reporting and harms

All AEs occurring from the time of consent until the end of the study will be recorded, including description, severity, duration, action taken, causality assessment (related/unrelated to intervention), and outcome. SAEs will be reported to the PI and the IRB within 24 h of awareness. The PI will determine causality. An annual safety report will be submitted to the IRB. All AEs will be listed and summarized in the final publication.

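### Adverse-event causality is compared between arms although the PI alone assigns it in an open-label trial, with arm-specific lists of expected reactions, so counts of related events can differ without a difference in harm

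*Protocol article*

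**What the plan says.** Four parts of the protocol article bear on this point.

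- **Safety outcomes** makes causality one of three attributes compared between arms: "The incidence, severity, and causality of AEs were compared between groups to comprehensively evaluate the safety of the interventions". It also sets a separate watch list for each arm. For press-needle: "Local skin reactions at the press-needle insertion sites were mainly monitored, including redness, itching, pain, rash, infection, and bleeding". For naproxen: "Adverse reactions related to NSAIDs were intensively monitored, including gastrointestinal reactions (nausea, stomachache, acid reflux, abdominal distension, gastrointestinal discomfort", followed by dizziness, headache and fatigue as neurological reactions, rash and itching as skin allergy, and liver and renal abnormalities. It adds that systemic events are recorded in both arms.
- **Adverse event reporting and harms** sets a two-level scale, "causality assessment (related/unrelated to intervention", and says who decides: "The PI will determine causality".
- **Blinding design** says: "This is an open-label trial. Participants and intervention providers will be aware of the group assignments". The masked roles are given as "outcome assessors and statisticians will remain completely unaware of the group assignments throughout the trial", with data managers added in the third item. The PI is not listed.
- **Exploratory and safety analyses** summarises adverse and serious adverse events by arm, system organ class and preferred term, and tests differences in event rates with Fisher's exact test. It names no test of related events.

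The Quality control section that follows data management adds: "An independent Data Monitoring Committee (DMC) is not established for this low-risk trial". The PI and the study coordinator review the data internally instead.

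**The concern.** A relatedness judgement combines what happened to the participant with what the assessing physician believes about the treatment. A comparison of related events between randomised arms is fair only if the second part works alike in both arms, and here nothing in the text makes it do so. Nausea or fatigue in a naproxen participant matches a list headed as drug reactions. The same symptom in a press-needle participant matches no list. Headache is the sharpest case, because it is the symptom of the disease under study and also a listed drug reaction in one arm.

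Safety and tolerability are stated aims in the Abstract and the Objectives, and the Discussion already describes press-needle as the better tolerated treatment. If the arms differ in related systemic events, a reader would take that as support for this claim, although it could come from attribution alone. Identical questioning in both arms would not remove the problem, because it arises after the event has been recorded.

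**Working it through.** **Step 1. The plan's own figure.** The Sample size section gives 30 evaluable per arm and 20% dropout. 30 / (1 − 0.20) = 37.5, rounded up to 38 per arm, and 2 × 38 = 76. This reproduces the stated total. The document gives no adverse-event rate and no attribution rate, so everything numerical below rests on assumed rates.

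**Step 2. The two lists side by side.**

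| Type of event | Named for naproxen | Named for press-needle |
|---|---|---|
| Gastrointestinal symptoms | yes | no |
| Dizziness, headache, fatigue | yes | no |
| Liver or renal abnormality | yes | no |
| Rash, itching | yes, as allergy | yes, as site reaction |
| Redness, pain, infection, bleeding at the site | no | yes |

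The asymmetry is real for gastrointestinal and neurological symptoms and for liver and renal findings. It does not hold for rash and itching.

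**Step 3. Model.** Let h be the true proportion of participants with a non-specific event, equal in both arms. Let aN and aP be the probabilities that such an event is called related under naproxen and under press-needle. Related incidence is h × aN in one arm and h × aP in the other. The chance of a two-sided Fisher p < 0.05 is found by summing the two binomial distributions over all tables. Any significant result is false, because h is the same in both arms.

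**Step 4. Results at h = 30%.**

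| aN / aP | Related incidence | Expected cases, 38 per arm | Significant, 38 per arm | Significant, 30 per arm |
|---|---|---|---|---|
| 50 / 50 | 15% vs 15% | 5.7 vs 5.7 | 2.4% | 1.7% |
| 60 / 40 | 18% vs 12% | 6.8 vs 4.6 | 6.4% | 4.2% |
| 60 / 30 | 18% vs 9% | 6.8 vs 3.4 | 13% | 8% |
| 70 / 20 | 21% vs 6% | 8.0 vs 2.3 | 36% | 24% |
| 80 / 10 | 24% vs 3% | 9.1 vs 1.1 | 71% | 52% |
| All events, any cause | 30% vs 30% | 11.4 vs 11.4 | 3.0% | 2.6% |

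Example for 70 / 20: 0.30 × 0.70 = 0.21 and 0.30 × 0.20 = 0.06, so 38 × 0.21 = 8.0 and 38 × 0.06 = 2.3 cases.

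**Step 5. Sensitivity to incidence.** At h = 20%, a 60 / 40 gap gives 3.3% (38 per arm) or 1.9% (30 per arm). At h = 15%, a 70 / 20 gap gives 8.3% or 4.0%, and 60 / 30 gives 2.9% or 1.4%. At h = 50% and 38 per arm, 60 / 40 gives 11.8%. Over h from 20% to 50%, the comparison of all events stays at 2.7% to 3.0% with 38 per arm.

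The distortion can thus be negligible or large, depending on an attribution gap that the document does not give.

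**The case against.** The strongest reply is that the statistical section already does most of what is needed. Its only named test is on adverse-event rates, which do not depend on attribution, and no test of related events is planned. This stands. The figures above illustrate what would happen if such a test were applied, and do not describe a planned analysis. It does not remove the point, because Safety outcomes still prescribes a causality comparison as part of the safety evaluation, and the statistical section neither withdraws it nor says that its rates are regardless of cause.

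Other replies stand in part:

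- The lists say what is monitored and are not a causality rule. That is correct, and each event still gets its own assessment. But the naproxen list is worded as drug-related reactions, and one person then makes a two-level call.
- Systemic events are recorded in both arms. This protects recording but not attribution.
- Nowhere is the PI said to be unmasked. It is an inference, though a strong one: the trial is open-label, the PI is not on the masked list, and judging relatedness to a needle or a tablet in practice requires knowing which was given.
- The trial is exploratory, and its limitations paragraph admits expectancy effects and operational bias. Cautious reading of p-values does not remove a systematic bias.
- Reporting relatedness by arm still puts two numbers side by side. That is so, but without a test or a safety conclusion they are not offered as evidence of a difference in harm.

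Two stronger readings are tempting. A reader might infer that related events will differ between arms. The document gives no rates from which that follows. A reader might also infer that the bias favours press-needle overall. That is plausible for systemic events only: site reactions would readily be called related to the needle, so total related events could be higher in that arm.

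**Conclusion.** The point holds in a limited form. A between-arm difference in related adverse events cannot be read as a difference in harm under this plan, and the plan nonetheless states that comparison as part of its safety evaluation. The defect is confined to the causality element in Safety outcomes and does not touch the Fisher test on event rates.

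Under the assumed 30% incidence with 38 per arm, false significance would be about 6% at 60 / 40 attribution and 36% at 70 / 20, against 3% for all events. With smaller gaps or fewer events it can fall to about 3% or lower. These figures assume equal true harm, one attribution probability per arm and one event per participant. The change is worth making because it removes a biased comparison at almost no cost.

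**What to change.** 1. In Safety outcomes, delete causality from the list of attributes compared between groups, leaving incidence and severity.
2. In Exploratory and safety analyses, state that between-arm comparisons of adverse and serious adverse events (incidence and severity) cover all events regardless of causality.
3. In the same place, state that the PI's relatedness judgements are reported by arm descriptively, with no between-arm test and no safety conclusion drawn from them.

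The cost is one deleted word and one or two sentences, with no new data, staff or visits. Individual causality assessment for safety reporting is unchanged.

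This does not cure a separate problem. Safety outcomes describes monitoring as intensive for drug reactions in one arm and as directed mainly at skin reactions in the other. Uneven ascertainment of that kind could also bias the comparison of all events, and it needs its own correction.
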